#### Patient-reported psychosocial outcomes

Our second aim is to explore trends and detectable between-group differences in psychosocial PROs at 12 weeks. Our primary PRO of interest is *Social Relationship Coping Efficacy (SRCE),* measured using the validated Cancer Behavior Inventory–Social Relationship Coping Efficacy subscale [54]. Ten items, on 1–9 Likert scale, assess confidence to engage in behaviors that maintain or enhance relationships in the context of illness. We also assess five secondary PROs. *Perceived Social Support* is measured using the Multidimensional Scale of Perceived Social Support [59]. This 12-item tool measures support from family, friends, and a significant other. *Quality of Life* is measured via the Patient-Reported Outcomes Measurement Information System (PROMIS) Pediatric Profile-25 (v2.0) [60]. This profile includes 25 items assessing health status across 7 domains: physical function mobility, anxiety, depressive symptoms, fatigue, peer relationships, pain interference, and pain intensity [61–64]; we also included an additional 4-items assessing family relationships (PROMIS Pediatric Family Relationships short-form v1.0) [65]. *Anxiety and depression* are measured using the Hospital Anxiety and Depression Scale [66]. *Self-perceived resilience* is measured using the 10-item Connor-Davidson Resilience Scale [67]. *Hope,* or the overall perception that one’s goals can be met, is measured using the 8-item Snyder Hope Scale [68].

### Data analysis and sample size

Conservatively assuming 30% attrition due to illness, death, or dropout, we anticipate recruiting 100 AYAs over 2 years, with an evaluable sample of 70 (*N* = 35 per arm). This sample size will provide a margin of error ± 11% at 95% confidence for an estimated rate of 70%; for a rate of 80%, the margin of error is ± 9% at 95% confidence. This pilot trial is not powered to detect efficacy; data will be used to demonstrate intervention feasibility and proof-of-concept and inform the design of future larger randomized trials including benchmarks for accrual, retention, and intervention adherence.

Primary statistical analyses will be conducted on an intention-to-treat basis to avoid confounding by non-random participant attrition. To determine feasibility and acceptability (Study Objective 1), benchmark proportions and descriptive statistics will be used to examine uptake and retention rates and AIM scores. To determine proof-of-concept (Study Objective 2), demographics, clinical characteristics, and PRO items will be summarized at each time point using descriptive statistics: frequencies and proportions for categorical variables, means and standard deviations for continuous variables, or the median and interquartile range if the distribution is markedly skewed. Categorical outcomes will be compared between arms using the chi-squared test, and continuous outcomes will be compared using two-sample *t*-tests. In addition, covariate-adjusted linear regression models will be used to compare PROs between study arms, in which study arm is the predictor of interest and the stratification factors, site and age, are the covariates. For PROs without an established minimal clinically important difference (MCID), we will define minimal important differences as ½ standard deviation based on comparison samples [69].

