### Outcomes

#### Feasibility and acceptability outcomes

Our first aim is to establish feasibility and acceptability of the PRISM-SN program. Our *a priori* feasibility outcomes include: (a) *uptake*, calculated as the proportion of AYAs enrolled out of total AYAs approached and (b) *retention*, calculated as the proportion of AYAs who remain in the study at 12 weeks out of total AYAs enrolled. PRISM-SN will be considered feasible if uptake is ≥ 70% and retention is ≥ 70%. We will also examine additional feasibility outcomes relevant to intervention delivery and adherence, including the number of sessions completed, session format and frequency, intervention length, and fidelity. *Acceptability *will be determined via the patient-reported Acceptability of Intervention Measure [58] at 12 weeks. This validated instrument includes 4 items such as “[program] meets my approval,” scored 1–5, with higher average scores reflecting more acceptability. PRISM-SN will be acceptable if ≥ 80% of AYAs on the intervention arm have an average score of ≥ 4 on this measure.

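### The stated margins of error (±11% and ±9%) rest on n = 70, which is the denominator of none of the three benchmark proportions; for acceptability the margin is about ±13%, not ±9%

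*Protocol article*

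**What the plan says.** All references are to the protocol article.

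**Data analysis and sample size.** The plan is "we anticipate recruiting 100 AYAs over 2 years", with attrition put at 30%, "with an evaluable sample of 70", or 35 per arm. It then says that this sample size gives a margin of ±11% "at 95% confidence for an estimated rate of 70%; for a rate of 80%, the margin of error is" ±9%. The same paragraph states that the pilot is not powered for efficacy, so these margins are the only quantitative support for the sample size.

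**Feasibility and acceptability outcomes.** Three benchmark proportions are defined:

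- Uptake, at least 70%: "calculated as the proportion of AYAs enrolled out of total AYAs approached".
- Retention, at least 70%: "calculated as the proportion of AYAs who remain in the study at 12 weeks out of total AYAs enrolled".
- Acceptability, at least 80%: the programme counts as acceptable if at least "80% of AYAs on the intervention arm have an average score of" 4 or more on the acceptability measure at 12 weeks.

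**The concern.** The two rates in the precision statement, 70% and 80%, are exactly the two benchmark levels, so a reader will take the margins as the precision of those benchmarks. The margins use the evaluable sample pooled over both arms, and no criterion is calculated on that group. Uptake is taken over everyone approached and retention over everyone enrolled. Acceptability is taken over the intervention arm only, because control participants do not receive PRISM-SN. For retention, the 70 evaluable participants are roughly the expected numerator (70 of 100).

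What is at stake is how much weight a pass or fail can bear when the larger trial is designed. With ±9% in mind, a reader would expect the acceptability result to separate a programme that meets the target from one well below it better than 35 respondents allow. For uptake and retention the stated ±11% errs the other way and undersells the design.

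**Working it through.** **Inputs.** From Data analysis and sample size: 100 recruited, 30% attrition, 70 evaluable, 35 per arm. From Randomization: 1:1 allocation, hence about 50 of the 100 in the intervention arm. From Feasibility and acceptability outcomes: the three definitions and their 70%, 70% and 80% levels. The number approached is not given. It cannot be below the 100 enrolled, and 100/0.70 ≈ 143 is the assumption if uptake is exactly 70%.

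**Formula.** 95% half-width = 1.96 × √(p(1 − p)/n).

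**Step 1: reproduce the stated figures.**

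- p = 0.70, n = 70: 1.96 × √(0.21/70) = 1.96 × 0.05477 = 10.7%, which rounds to 11%.
- p = 0.80, n = 70: 1.96 × √(0.16/70) = 1.96 × 0.04781 = 9.4%, which rounds to 9%.

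Only n from 69 to 73 gives both rounded figures. Neither 100 (9.0% and 7.8%) nor 35 (15.2% and 13.3%) does. The margins therefore rest on the pooled evaluable sample.

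**Step 2: put each criterion on its own denominator.**

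| Criterion | Rate | Denominator | Calculation | Margin | Stated |
|---|---|---|---|---|---|
| Acceptability | 80% | 35 evaluable, intervention arm | 1.96 × √(0.16/35) | ±13.3% | ±9% |
| Acceptability, all allocated | 80% | about 50 | 1.96 × √(0.16/50) | ±11.1% | ±9% |
| Retention | 70% | 100 enrolled | 1.96 × √(0.21/100) | ±9.0% | ±11% |
| Uptake | 70% | about 143 approached (assumed) | 1.96 × √(0.21/143) | ±7.5% | ±11% |

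For uptake the range is ±9.0% with 100 approached to ±6.4% with 200.

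**Step 3: check that the approximation is not the cause.** For 28 of 35, which is exactly 80%, the Wilson interval is 64.1% to 90.0% and the exact interval 63.1% to 91.6%. The Wilson half-width is 12.9%, so the conclusion is the same. The ratio of the n = 35 margin to the n = 70 margin is √(70/35) = √2 ≈ 1.41.

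**Step 4: what this means for the acceptability rule.** Suppose the true proportion scoring 4 or more were 70%, ten points below target. The binomial probability of still meeting the 80% rule is 13% with 35 respondents (28 or more) and 4% with 70 respondents (56 or more). The risk of a false pass at that value is about three times what a sample of 70 would give.

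**The case against.** The strongest reply is that nothing has been miscalculated. The sentence names no outcome. It gives generic precision for two rates at the evaluable sample size, and both figures are right for n = 70. No confidence limit enters a decision either, since all three criteria are point thresholds assessed with descriptive statistics. For uptake and retention, the two criteria that define feasibility, the stated margin is too wide and so misleads nobody into overconfidence. Finally, 35 is not the only possible denominator for acceptability. Primary analyses are by intention to treat, about 50 are allocated to the intervention arm, and those who stop sessions may still answer the follow-up survey.

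Much of this stands. The fault is the base and not the arithmetic, the link between rates and criteria is inferred, the uptake and retention figures are conservative, and no pass or fail rule changes. It does not rescue the ±9%. The rates coincide with the benchmark levels, and acceptability is the only criterion at 80%. Under either reading its denominator is one arm, so the margin lies between ±11.1% and ±13.3%. The lower figure needs an answer from all of about 50, whereas the plan itself expects 35 evaluable per arm for a patient-reported measure at 12 weeks. The abstract's statement that 70 will enroll and complete data collection does not help, because one arm would still hold about 35.

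**Conclusion.** The concern holds. The precision statement is correct for a sample of 70, but 70 is not the denominator of uptake, retention or acceptability as the article defines them. The part that matters most is acceptability: about ±13.3% against the stated ±9%, or ±11.1% on the most favourable denominator. Retention (±9.0%) and uptake (about ±7.5%) are more precise than the stated ±11%.

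This rests on three assumptions: that the 70% and 80% rates refer to the benchmarks at those levels; that acceptability will be calculated on the 35 evaluable intervention participants; and, for the uptake figure only, that about 143 are approached. Because these margins are the sample-size justification, they need correcting, although no threshold, analysis or enrolment target depends on them.

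**What to change.** In Data analysis and sample size, replace the precision sentence with one margin per criterion, each with its denominator:

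- uptake: about ±7.5% at 70%, assuming about 143 approached, with the assumption stated (±9.0% to ±6.4% for 100 to 200 approached);
- retention: ±9.0% at 70%, with 100 enrolled;
- acceptability: about ±13% at 80%, with 35 intervention-arm respondents.

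If retention is also to be reported by arm, about 50 per arm gives 1.96 × √(0.21/50) = ±12.7%; this is optional, since the criterion is defined over all enrolled.

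The cost is one sentence. The acceptability figure becomes less favourable and the other two more favourable. Enrolment, benchmarks and conduct do not change.

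### Intention-to-treat is credited with avoiding attrition bias, but it gives no protection for participants who have no 12-week survey

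*Protocol article*

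**What the plan says.** All quotes are from the protocol article, section Data analysis and sample size.

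- Principle and its stated purpose: "Primary statistical analyses will be conducted on an intention-to-treat basis to avoid confounding by non-random participant attrition".
- Expected loss: "Conservatively assuming 30% attrition due to illness, death, or dropout, we anticipate recruiting 100 AYAs over 2 years", "with an evaluable sample of 70", that is 35 per arm.
- Methods for the PROs: "continuous outcomes will be compared using two-sample" t-tests, and "covariate-adjusted linear regression models will be used to compare PROs between study arms", with site and age as the named covariates.

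Other sections of the article bear on this:

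- Participants and procedures: PROs are collected at baseline and once more, at 12 weeks. Participants may be taken off study if activities are not completed in time or if they cannot be reached for more than 4 weeks.
- Randomization: allocation follows the baseline survey and is not blinded to participants or staff.
- PRISM-SN intervention: a participant who asks to stop sessions may stay in the study and still complete the follow-up survey.

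**The concern.** Intention-to-treat answers the question of which arm a person is counted in. It does not supply an outcome that was never collected. The sentence names non-random attrition as the problem and intention-to-treat as the remedy, and the remedy does not act on the main part of that problem, namely people with no 12-week score. The same section attributes attrition to illness, death or dropout, causes that may well be related to psychosocial outcomes.

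Loss could plausibly differ between arms. The trial is unblinded, and the intervention arm has more activities to complete within the allowed time (five modules and a family meeting). Proof-of-concept is read from the 12-week PRO comparison, which is also meant to inform a larger trial. A reader who takes the sentence at face value would regard those differences as protected against attrition when, as described, they are not.

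**Working it through.** **1. Reproduce the plan's figures.** Inputs: 100 recruited, 30% attrition, rates of 70% and 80% (Data analysis and sample size).

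- Evaluable sample: 100 × (1 − 0.30) = 70.
- Half-width = 1.96 × √(p(1 − p)/n).
- n = 70: p = 0.70 gives 10.74%; p = 0.80 gives 9.37%. These round to the stated 11% and 9%.
- n = 100: 8.98% and 7.84%, which do not match.

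The figures reproduce, and the stated precision rests on the 70 evaluable participants.

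**2. Who enters the PRO comparison.** There is one post-baseline survey. A t-test on the 12-week score, or a linear regression of it on arm, site and age, uses only observed scores unless missing values are filled in. As described, the comparison therefore uses those with a 12-week score.

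**3. Size of the possible bias.** Let m be the proportion missing in an arm and g the amount, in SD, by which those missing would have scored worse than completers. If C is the completers' mean, the mean over everyone in the arm is (1 − m)C + m(C − g) = C − mg. The bias in the arm difference (subscript 1 for PRISM-SN, 0 for usual care) is therefore

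bias = m₁g₁ − m₀g₀.

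The documents give no g and no attrition by arm. The values below are assumptions.

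| m₁ | m₀ | g₁ | g₀ | bias (SD) |
|---|---|---|---|---|
| 0.30 | 0.30 | 0.3 | 0 | 0.09 |
| 0.30 | 0.30 | 0.5 | 0 | 0.15 |
| 0.30 | 0.30 | 1.0 | 0 | 0.30 |
| 0.30 | 0.30 | 0.5 | 0.5 | 0 |
| 0.30 | 0.30 | 1.0 | 1.0 | 0 |
| 0.40 | 0.20 | 0.5 | 0.5 | 0.20 − 0.10 = 0.10 |
| 0.40 | 0.20 | 1.0 | 1.0 | 0.40 − 0.20 = 0.20 |

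A positive value overstates the benefit of PRISM-SN. Exchanging the arms reverses the sign, so the bias could equally hide a benefit.

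**4. Check with a smooth dropout mechanism.** Scores were simulated as standard normal with no true arm difference, and the chance of responding followed a logistic function of the score (slope 0.5 or 1 per SD). With 70% retained in each arm and the dependence in one arm only, the completers' difference was 0.142 and 0.251 SD. With 60% and 80% retained and the same dependence in both arms, it was 0.094 and 0.162 SD. With 70% retained and the same dependence in both arms, it was zero within simulation error. The pattern agrees with step 3.

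**5. Scale.** Where no clinically important difference is established, the plan uses ½ SD. Against that, 0.09, 0.15 and 0.30 SD are 18%, 30% and 60%. For comparison, the 95% half-width of a difference with 35 per arm is about 1.96 × √(2/35) = 0.47 SD.

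**The case against.** Several stronger readings are tempting, and the article does not support them.

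- *The plan specifies a complete-case analysis.* It never says so. That is inferred from the named methods and the evaluable 70. An SAP or full protocol that is not shown may add a missing-data method, and its absence from an article is no fault. The sentence would still be wrong, because any protection would come from that method and its assumptions.
- *Thirty of 100 randomized participants will lack an outcome.* The 100 are recruited, and randomization comes after the baseline survey, so some loss may precede it. The 30% is also described as a conservative allowance. Thirty per cent missing per arm is thus an upper-end reading, and for a given gap the bias shrinks in proportion to m.
- *Intention-to-treat protects against nothing here.* It does protect against dropping people who stop sessions but complete the survey, which the protocol expressly allows. The gap concerns lost outcomes only.
- *The PRO differences will be biased.* They could be. The bias is zero if loss is equal and alike in both arms, and the smaller illustrative biases are small beside sampling error. The ½ SD yardstick applies only to PROs without an established threshold, and the article does not say whether social relationship coping efficacy is one of them.
- *A likelihood-based model would settle the matter.* With one baseline and one follow-up score it rests on data being missing at random given baseline, much as a baseline-adjusted regression does.

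The pilot is also not powered for efficacy, and its numeric criteria are uptake, retention and acceptability. All of this limits the severity. None of it makes the stated purpose of intention-to-treat correct.

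**Conclusion.** The point stands as a wrong statement in the text: the plan claims a property that analysis as randomized does not have for participants without a 12-week survey. The illustrative 0.09 to 0.30 SD rests on 30% missing in each arm and on an assumed gap of 0.3 to 1.0 SD in one arm only. Other assumptions give anything from zero upward, in either direction. The conclusion about the sentence does not depend on those values. Severity is moderate: the feasibility and acceptability criteria do not rest on the between-arm PRO difference, but the proof-of-concept reading does.

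**What to change.** 1. Replace the sentence with a plain statement that participants are analysed in the arm to which they were randomized, and remove the claim about attrition.
2. Include the baseline PRO in the primary model, either as a baseline-adjusted regression with multiple imputation by arm or as a constrained longitudinal model. State that it assumes data are missing at random given baseline and covariates. Site, age group and treatment intensity are already collected and can inform imputation. Sessions completed can do so in the intervention arm only.
3. Add one delta-adjusted sensitivity analysis for non-random loss, with the range of shifts justified in advance.
4. Report attrition, reasons and deaths by arm, and do not impute scores after death.

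If the SAP already contains items 2 to 4, only the sentence needs changing. Otherwise the cost is modest extra analysis work, with no new data collection and no change to sample size.

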**Methods:**

We anticipate 70 AYAs will enroll and complete data collection at two sites: Seattle Children’s Hospital and UPMC Children’s Hospital of Pittsburgh. Eligible AYAs are ages 12–25 years old; diagnosed with a new malignancy < 6 months; treatment plan includes chemotherapy and/or radiation; and are English-speaking. Enrolled AYAs are randomized 1:1 to receive PRISM-SN or usual care and complete surveys at baseline and 12-week follow-up. PRISM-SN includes 5 sessions (4 standard PRISM modules + new SN module) teaching behavioral skills associated with psychosocial wellbeing. Sessions are delivered 1:1 by a trained coach, in person or virtually, 1–2 weeks apart. Feasibility will be defined based on uptake, retention, and patient-reported intervention acceptability. Proof-of-concept will be defined based on clinically meaningful change and detectable differences in PROs at 12 weeks, including social relationship coping efficacy (primary PRO of interest), social support, quality of life, resilience, anxiety, depression, and hope. Descriptive statistics and covariate-adjusted regression models will be used to assess feasibility outcomes and examine trends and between-group differences in PROs across study arms.

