Participant timeline is described in Fig. 1. Enrolled participants on both arms complete a survey containing a demographic questionnaire and a PRO battery at baseline (pre-randomization) and at 12-week follow-up. Surveys are administered via Research Electronic Data Capture (REDCap) [57] or paper and pencil upon request and must be completed within 4 weeks. Incentives of $25 and $50 are provided for baseline and follow-up surveys, respectively, and participants on both arms receive a small non-monetary incentive (e.g., tote bag or water bottle with the study logo) during their participation. To promote retention and follow-up, study staff contact participants via email, phone, or in-person check-ins to notify them of an upcoming survey due date and confirm how they would like to complete the survey (e.g., email link, study tablet provided during clinic visit, paper and pencil). Thereafter, staff provide weekly reminders for outstanding surveys. Clinical information is abstracted from electronic health records each month throughout the study period, including diagnosis, diagnosis date, treatment modalities and intensity, any pre-existing or current psychiatric diagnoses, and any formal psychological treatment received during study participation. Participants may be taken off study if they request to withdraw, do not complete study activities within the specified timeframe, are unable to be reached by study staff for > 4 weeks, or are deceased before completing study activities. For participants who request to withdraw from the study, study staff ask for and document reasons for withdrawal.

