### Randomization

Following baseline survey completion, AYAs are randomized 1:1 to the intervention or the control arm, with strata defined by age group (12–17 vs. 18–25 years) and study site. The randomization was constructed by the study statistician using a permuted blocks scheme with randomly varying block sizes. Study staff administer randomization assignments using REDCap [57] and maintain a randomization log; staff do not have access to the random allocation sequence. Blinding of study staff or participants is not feasible or practical given the nature of the intervention; however, study statisticians will be blinded to group assignment for data analysis.

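### The between-arm PRO comparison adjusts for site and age only; the baseline PRO score, available for everyone randomized, is left out of the model and precision is lost

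*Protocol article*

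**What the plan says.** All references are to the Protocol article.

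- **Data collection** (Participants and procedures): "Enrolled participants on both arms complete a survey containing a demographic questionnaire and a PRO battery at baseline (pre-randomization) and at 12-week follow-up".
- **Order of events and strata** (Randomization): "Following baseline survey completion, AYAs are randomized 1:1 to the intervention or the control arm". The baseline survey therefore precedes allocation for everyone. The scheme is stratified, "with strata defined by age group (12–17 vs. 18–25 years) and study site", so baseline PRO is not a stratification factor.
- **Between-arm analysis** (Data analysis and sample size): the simple comparisons are described by "Categorical outcomes will be compared between arms using the chi-squared test, and continuous outcomes will be compared using two-sample", the test for continuous PROs being the t-test. A linear regression is planned as well, "in which study arm is the predictor of interest and the stratification factors, site and age, are the covariates".
- **What the PROs are for** (Abstract, Methods): "Proof-of-concept will be defined based on clinically meaningful change and detectable differences in PROs at 12 weeks". The section on patient-reported psychosocial outcomes describes the second aim as exploring trends and between-group differences at 12 weeks.
- **Yardstick** (Data analysis and sample size): half a standard deviation, for PROs that have no established minimal clinically important difference.

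In the analysis section, baseline PRO values appear only in the descriptive summaries by time point. The article mentions no baseline adjustment, change-score outcome or repeated-measures model for the comparison between arms.

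**The concern.** The article names its covariates, so this is a model that has been stated, not a detail left open. The list omits the variable that would usually be expected to predict a 12-week score best, namely the same score at baseline, even though the design guarantees that the baseline survey comes before allocation.

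Two things are at stake, both in the proof-of-concept comparison. First, the confidence intervals may be wider than the data require, in a trial with only 35 evaluable participants per arm. Second, stratifying by site and age group does not balance the PROs themselves. Part of any chance baseline difference between arms therefore carries into an unadjusted 12-week difference, which is then read against a half-SD yardstick.

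The dependent variable is also unclear. The abstract speaks of change, the outcomes section speaks of differences at 12 weeks, and the analysis section says only that PROs are compared.

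**Working it through.** **Inputs from the article.** 70 evaluable participants, 35 per arm; 100 recruited with 30% attrition; minimal important difference 0.5 SD where none is established.

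**Input assumed.** The correlation r between baseline and 12-week score is not in the article, so a range of 0.3 to 0.7 is used. Strictly, it is the correlation that remains after site and age are accounted for. Equal SDs at both times are also assumed, and results are in SD units.

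**Step 1: the plan's own figures.** 70/(1 − 0.30) = 100. The margin of error is 1.96 × √(p(1 − p)/70), which gives 10.7% at p = 0.70 and 9.4% at p = 0.80. These agree with the stated ±11% and ±9%. The article gives no corresponding precision for the PROs.

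**Step 2: unadjusted 12-week comparison.** SE = √(2/35) = 0.239 SD. With the t quantile on 68 degrees of freedom (about 1.996), the 95% half-width is 1.996 × 0.239 = 0.48 SD. The normal quantile would give 0.47.

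**Step 3: add the baseline score.** SE = √(1 − r²) × √(2/35), so the variance falls by r². The equivalent unadjusted sample is 70/(1 − r²).

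| Assumed r | Variance cut | 95% half-width (SD) | Equivalent unadjusted total n |
|---|---|---|---|
| none (baseline omitted) | – | 0.48 | 70 |
| 0.3 | 9% | 0.46 | 77 |
| 0.5 | 25% | 0.41 | 93 |
| 0.6 | 36% | 0.38 | 109 |
| 0.7 | 49% | 0.34 | 137 |

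**Step 4: if change scores were meant.** The variance of a change score is 2(1 − r) times that of the 12-week score, so the half-width is 0.477 × √(2(1 − r)). This gives 0.56 at r = 0.3, 0.48 at 0.5, 0.43 at 0.6 and 0.37 at 0.7. The baseline-adjusted variance is (1 − r²)/(2(1 − r)) = (1 + r)/2 of the change-score variance: 0.65, 0.75, 0.80 and 0.85. Adjustment is still better throughout this range. At r = 0.6 and 0.7 its advantage shrinks to 20% and 15% of the variance.

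**Step 5: chance imbalance.** With 35 per arm, the baseline difference between arms also has SE 0.239 SD. Given such a difference, the unadjusted 12-week estimate is expected to shift by r times it. A one-SE imbalance shifts it by 0.5 × 0.239 = 0.12 SD at r = 0.5, and by 0.7 × 0.239 = 0.17 SD at r = 0.7. Those are 24% and 33% of the half-SD yardstick.

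**Step 6: simulation (20,000 runs each at r = 0.5 and 0.7).** Both estimators averaged zero when there was no effect. Their empirical SEs were 0.239 unadjusted against 0.209 adjusted at r = 0.5, and 0.239 against 0.173 at r = 0.7. The unadjusted estimate correlated with the baseline imbalance at 0.50 and 0.69; the adjusted estimate correlated at about zero.

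**The case against.** The strongest reply is that this is a pilot. The article says it is not powered for efficacy, and the PROs belong to an exploratory second aim. The feasibility and acceptability criteria do not depend on this model. That is true and it limits the weight of the point. It does not remove it, because the plan still tests PROs between arms and judges proof-of-concept on them.

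A second reply is that the dependent variable may be change from baseline, which would use the baseline score. The article does not exclude this, and Step 4 shows that the gain would then be smaller for r above 0.5. This stands as a limit on the size.

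Third, the 0.48 SD reference belongs to the t-test. The planned regression already adjusts for site and age and may do somewhat better. That also stands, and it is why r should be read as a partial correlation.

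Four stronger readings are tempting, and the document does not support them:

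- *The planned comparison is biased.* It is not, as far as randomization is concerned; the imbalance is chance error.
- *A baseline imbalance passes in full into the effect.* The chance that a baseline difference exceeds 0.25 SD is about 30%, and a reader might take that as a 30% chance of shifting the effect by half the yardstick. Only r times the imbalance carries over. A shift above 0.25 SD needs an imbalance above 0.25/r, with probability about 4%, 8% and 14% at r = 0.5, 0.6 and 0.7.
- *The t-test is the lead analysis.* The article mentions it first but ranks neither method, and reporting both is ordinary practice.
- *The PRO estimate will set the next trial's sample size.* The design inputs that the article names are benchmarks such as accrual, retention and adherence; it does not name the PRO effect.

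**Conclusion.** The point holds as a loss of precision. The stated covariates leave out a baseline score that the design collects before allocation, and the form of the outcome is not fixed. Against an unadjusted 12-week comparison, adding baseline would cut the variance by about 9% at r = 0.3, rising to 49% at r = 0.7. The 95% half-width would go from 0.48 SD to between 0.46 and 0.34 SD. A one-SE chance imbalance would move the unadjusted estimate by about 0.12 to 0.17 SD for r between 0.5 and 0.7, against a half-SD yardstick.

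That baseline is missing from the named covariates is plain from the text. The size of the gain is less certain: it rests on an assumed correlation, on 35 evaluable participants per arm, and on the 12-week score being the outcome. At the low end of the range the gain is small. This is a worthwhile improvement to an exploratory aim, not a flaw that undermines the trial.

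**What to change.** In Data analysis and sample size, state that the main between-arm comparison for each PRO is a linear regression of the 12-week score on study arm, that PRO's baseline score, site and age group. Report the adjusted mean difference with its 95% CI and set it against that PRO's minimal important difference. The unadjusted t-tests may stay, labelled descriptive. This wording also settles whether the outcome is the 12-week score or change.

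The cost is a sentence or two of text and one degree of freedom per model. No new data are needed, since the baseline survey is already completed before randomization.
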